**Methods:**

This study will be an unblinded cluster-randomized, matched controlled trial conducted among 8200 stable, HIV-infected individuals age 18 years and older on ART in Malawi and Zambia, to compare three ART dispensing intervals on the outcomes of retention in care (primary outcome), virologic suppression, and cost-effectiveness. Thirty clusters will be matched according to country, facility type, and ART cohort size and randomized to one of three study arms: standard of care, 3-month dispensing, and 6-month dispensing. Study participants will be followed, and outcomes will be measured at 12, 24, and 36 months. A subset of participants (n = 240) and providers (n = 180) will also participate in qualitative interviews to evaluate feasibility and acceptability of different ART dispensing intervals.

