### Blinding and allocation

Random assignment of matched clusters will be determined by computer. Clusters will be matched based on available information that could potentially predict outcomes, including ART cohort size and region. Matched clusters will then be randomly allocated with one receiving the 3-month intervention, one the 6-month intervention, and one the control condition. Allocation will be completed by the study analyst. Clusters will then be informed of the allocation. No attempt will be made to blind the sites or patients to their allocated group, as both providers and patients will be aware of the amount of medication dispensed and the timing between appointments.

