#### Entry visit data collection

All patient baseline data will be collected in the entry visit, which may come immediately after screening for eligible patients, or may take place at the next visit when a viral load result is available. Two types of data will be collected at the entry visit. First, the participant’s medical record will be reviewed to collect clinical history, including date of HIV diagnosis, date of ART initiation, use of CPT and/or IPT, and history of ART clinic visits and ART dispensing intervals in the prior 12 months. The second type of data will come from an interview with the patient. In the interview, the study interviewer will obtain sociodemographic information about the participant, including gender, highest level of education, household composition, employment status, HIV disclosure status, and travel and opportunity costs related to the participant’s ART clinic visits. After completion of the entry visit data collection, the participant will complete her or his routine clinic visit with site providers and receive ART dispensing as per the site randomization. If CPT and/or IPT dispensing is standard of care for the facility, CPT and/or IPT will also be provided as per the randomized dispensing interval.

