### Data analysis

#### Primary outcome

Our primary outcome, which is the basis for our sample size estimates and primary analysis, is retention in care at 12 months after study enrollment. Data analyses will begin with descriptive measures about the study population stratified by treatment arm and by facility and presented as medians and interquartile ranges for continuous measures and proportions for categorical variables. These measures will be used to look for large variations by facility and for imbalances between study arms.

We will perform an intention-to-treat analysis for the primary outcome of retention. Our analysis will use a log-linear generalized estimating equation to estimate the risk ratios and associated 95% confidence interval for the effect of each intervention arm compared to standard of care. We will specify facility-level clustering to account for the study design and estimate robust standard errors using an unstructured correlation matrix. Should we identify any baseline imbalances between study arms, we will adjust for these in our multivariable model and report adjusted risk ratios and corresponding 95% confidence intervals.

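### Facilities are randomised within ten matched triplets, but the primary model omits the triplet and adjusts only for observed imbalance, so matching's precision is discarded and the adjusted model is not fixed in advance

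*Protocol article*

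**What the plan says.** The abstract (Methods) describes the design: "Thirty clusters will be matched according to country, facility type, and ART cohort size and randomized to one of three study arms". Blinding and allocation gives the reason for matching, "Clusters will be matched based on available information that could potentially predict outcomes, including ART cohort size and region", and the restriction on the randomisation: "Matched clusters will then be randomly allocated with one receiving the 3-month intervention, one the 6-month intervention, and one the control condition". With 30 facilities and three arms, that makes 10 triplets.

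The Primary outcome section under Data analysis sets the model: "Our analysis will use a log-linear generalized estimating equation to estimate the risk ratios and associated 95% confidence interval". It then says how the design is handled: "We will specify facility-level clustering to account for the study design and estimate robust standard errors using an unstructured correlation matrix". It names no term for triplet, country, facility type, cohort size or region.

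Baseline covariates are chosen from descriptive tables by arm and facility ("These measures will be used to look for large variations by facility and for imbalances between study arms"), under the rule "Should we identify any baseline imbalances between study arms, we will adjust for these in our multivariable model". No covariate and no threshold for imbalance is named.

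**The concern.** There are two linked problems.

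First, the randomisation is restricted within triplets, but the stated account of the design stops at the facility. If the matching factors do predict retention, facilities in the same triplet resemble each other. The difference between arms is then more precise than a model without triplets reports, and the benefit of matching never reaches the confidence interval.

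Second, the covariate rule responds to imbalance rather than to prognostic value. A factor improves precision because it predicts retention, whether or not it happens to differ between arms. The trigger is also unlikely to bring the matching factors in, because matching makes the arms alike on exactly those factors. And because the arm-level tables are read before the covariates are chosen, the adjusted model is settled by the data.

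**Working it through.** **Inputs.** From Sample size: failure 5%, margin 7.5 − 5 = 2.5 points, one-sided 5%, power 90%, ICC 0.004, 271 per cluster. Clusters per arm: k = 30/3 = 10. Assumed, because the article gives no matching correlation: f, the share of between-facility variance explained by the triplets, taken from 0 to 75%.

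**1. The plan's own figure.** Unpooled, with 5% failure in both arms: n = 2 × 0.0475 × (1.645 + 1.282)² / 0.025² ≈ 1302 per arm before clustering. With k fixed, m = n(1 − ICC)/(k − n × ICC) = 1302 × 0.996/(10 − 5.208) = 270.6, so 271, and 271 × 30 = 8130. The figure reproduces, and the formula contains no matching term.

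**2. Variance of a facility's proportion.** Between: 0.0475 × 0.004 = 0.000190. Within: 0.0475 × 0.996/271 = 0.000175. Total V = 0.000365, so 52% lies between facilities. That is the part matching can act on.

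**3. Standard error of the difference between two arms.** Triplets ignored: √(2V/10) = 0.854 points. True, because triplet effects cancel within sets: √(2V(1 − 0.521f)/10).

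| f | true SE (points) | SE ignoring triplets ÷ true SE |
|---|---|---|
| 0 | 0.854 | 1.00 |
| 25% | 0.796 | 1.07 |
| 50% | 0.734 | 1.16 |
| 75% | 0.666 | 1.28 |

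**4. Small-sample-corrected analysis.** Simulated trials of 10 triplets, testing cluster means against the 2.5-point margin: t on 27 df ignoring triplets, t on 18 df with triplet terms. Repeated runs of at least 100,000 trials agree to about 0.1 point on the error rate.

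| f | true one-sided error at nominal 5%, triplets ignored | power with 95% CI, ignored | power with 95% CI, modelled |
|---|---|---|---|
| 0 | 5.0% | 81% | 79% |
| 25% | 4.0% | 82% | 84% |
| 50% | 2.9% | 84% | 90% |
| 75% | 2.1% | 86% | 94% |

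With triplets modelled, the error stays at 5% throughout. These powers start below the planned 90% mainly because a 95% CI corresponds to one-sided 2.5%, whereas the sample size used 5%; that is not part of this point. At one-sided 5% the figures are 88.8% ignored and 88.0% modelled at f = 0, and 91.8% and 94.9% at f = 50%. A check with binomial data on the log risk-ratio scale shows the same pattern: 95% CI coverage at f = 50% is 97.2% ignored and 94.8% modelled.

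**5. Uncorrected robust SE with normal quantiles.** This is the literal reading, since the article mentions no correction.

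| f | 95% CI coverage, triplets ignored | one-sided error at nominal 5% |
|---|---|---|
| 0 | 92.1% | 6.9% |
| 25% | 93.8% | 5.6% |
| 50% | 95.6% | 4.3% |
| 75% | 96.9% | 3.1% |

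Adding triplet terms to this uncorrected SE gives coverage of about 85% and one-sided error of about 11% at every f. The reason is that 30 facility means less 12 fitted parameters leave 18 df, so the raw sandwich variance averages 18/30 = 0.60 of its target. Without triplet terms it averages 9/10.

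**The case against.** The strongest objection is that the planned analysis is a GEE with robust SEs, not a t-test on cluster means. Read literally, with no correction, its intervals are not generally too wide: step 5 shows under-coverage at f of 25% or less and roughly nominal coverage at 50%. This stands. A reader might infer from the missing triplet term that the published intervals will be too wide, and the article does not support that across the plausible range. Two errors of opposite sign cancelling at an unknown f is not a reason to keep either, however.

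The same objection shows that adding triplet terms alone would do harm in a non-inferiority trial. That also stands and is built into the fix.

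A reader might also infer a risk of false non-inferiority or an undersized trial. Omitting effective matching is conservative, leaves the arm estimate almost unchanged in a balanced design, and does not touch the sample size, which was computed as unmatched. What is lost is extra precision that the plan never claimed.

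On covariates, the article says adjusted ratios will be reported, not that they replace the unadjusted ones. That the primary result will be selected after the tables are seen is therefore one possible reading, not a stated intention. An article may also leave the covariate list to a fuller document. The trigger itself, though, is stated here, and so is the way the design enters the model.

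**Conclusion.** The point holds as a mismatch between the randomisation and the stated model, together with an adjustment rule that depends on the data. With a corrected SE, omitting the triplets costs about 2 points of power with a 95% CI if they explain a quarter of between-facility variance, about 6 points at half and about 8 at three quarters. It saves 1 to 2 points if they explain nothing. The true one-sided error falls from 5% to about 2% over the same range.

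These sizes rest on the plan's ICC of 0.004, equal clusters of 271, 5% failure and the assumed f. The article says only that the matching factors might predict outcome. The direction is conservative under a corrected SE. Under an uncorrected one the small-sample bias partly or fully offsets it, so no general claim about interval width is warranted. This is a change that should be made, not a threat to the trial's validity.

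**What to change.** 1. Include the matched triplet, or the matching factors, as fixed terms in the primary model whatever the baseline tables show. List the factors once: the abstract gives country, facility type and cohort size, while Blinding and allocation gives cohort size and region as examples.
2. In the same sentence, require a small-sample correction: a bias-corrected robust SE with a t reference on about 18 df (9 × 2 for ten triplets and three arms), or a matched cluster-level analysis. Item 1 should not be adopted without this.
3. Replace the imbalance trigger with prognostic entry-visit covariates fixed in advance. Candidates already collected include gender, date of ART initiation and "history of ART clinic visits and ART dispensing intervals in the prior 12 months".
4. State which estimate is primary, and keep the version without those covariates as a sensitivity analysis.

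The cost is wording and a modest change to the analysis code. No new data are needed and the 271 per cluster stands. If matching proves uninformative, the triplet terms cost about 0.8 points of power at one-sided 5% (88.8% to 88.0%) and about 1.5 points with a 95% CI.

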#### Secondary outcomes

Our study has not been powered to look at secondary aims, but we expect to have enough power to explore differences in secondary endpoints. The analytic methods for the secondary outcome of virologic suppression will be identical to those described above for the primary outcome of retention. For qualitative secondary outcomes of patient and provider feasibility and acceptability of dispensing intervals, interviews will be transcribed by trained personnel. Interviews will be analyzed in Atlas.ti v.6.2 using thematic analysis. Two investigators will code the first five to ten interviews by themes and compare coding to reach a consensus. A codebook will be developed, and two individuals will independently code all transcripts and compare codes to reach a consensus. For each theme, we will describe the range, central tendency, and context in which each theme emerges. This process will be done separately for participants and providers.

Cost-effectiveness will be assessed as the average cost per patient achieving the primary outcome in each arm. Cost will be estimated using micro-costing methods developed by the investigators and widely published [12–14]. Costs will be reported as means with 95% confidence intervals and medians with IQRs. Using the average cost per patient, we will then estimate the cost per outcome achieved in each arm. We will compare average cost/patient retained in care across the three study arms, initially at 12 months and again at 24 and 36 months. The annual cost of providing ART under each of the three strategies evaluated (independent of outcomes) for the overall HIV program budget in each country will be estimated by combining the cost per patient treated under each strategy, study data on the proportions of all ART patients at study clinics who are eligible for each dispensing interval, and up-to-date, published or reported estimates of total numbers of patients on ART in each country.

To estimate the costs to patients of obtaining ART, we will use baseline patient interview data to calculate an average cost per clinic visit, including transport fares, food and accommodation while away from home, lost wages, and substitute labor. For each participant, the number of clinic visits made per 12-month period for any HIV-related reason will then be multiplied by the cost per visit. We will estimate and compare the average cost per patient of obtaining care in each study arm.

Finally, we will explore clinic resource allocation to determine the effects of the dispensing interval on patients’ access to care. We will use two proxy measures to analyze access. First, we will estimate and compare the average waiting time and/or total time in clinic among patients seeking HIV care in each arm of the study. Second, we will use aggregate, clinic-level data to ascertain whether the quantity or mix of services provided by each study site changes between the last month before the start of the study and the first month of year 2 of the study. While neither of these measures is a perfect indicator of access, both will provide some indication of the availability of both HIV care and care for non-HIV conditions.

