Secondary study outcomes include virologic suppression, cost-effectiveness, and feasibility and acceptability to patients and to providers and will be measured at 12, 24, and 36 months. Viral load data will be obtained from medical records based on any available data recorded during the prior year. Cost-effectiveness will be analyzed from both patient and health system perspectives by surveying participants at enrollment about time and costs associated with each clinic visit and by creating inventories of all resources and costs to the facility and health system for each patient visit. Feasibility and acceptability will be measured by conducting qualitative in-depth interviews with a subset of 240 participants (120 per country) and 180 providers (90 per country) evenly balanced among the three study arms. A flowchart of the study is provided in Fig. 1. Our main hypothesis is that 6-month ART dispensing will be non-inferior to 3-month intervals for retention and virologic suppression, but that 6-month intervals will be cost-effective compared to 3-month intervals.

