It is possible that Malawi and Zambia will revise their HIV treatment guidelines during study follow up, including extending dispensing intervals to 4 months or longer. In Malawi, IPT rollout in high-burden TB districts is anticipated during the first year of the study, and this will result in patients returning to clinic for extra visits to adhere to the IPT monitoring schedule (monthly for the first 3 months of treatment). These national guideline changes will be captured at the level of individual participant data and accounted for in our analyses, but they may influence our ability to measure intended study outcomes. Finally, the study will be working alongside Ministry of Health in both Malawi and Zambia to ensure that sites randomized to 6 months will have adequate supplies of ART, CPT, and IPT. Should countries adopt 6-month dispensing, this high level of support would be unlikely to be available at all sites, resulting in potential challenges with procurement, supply chain, and/or storage.

Despite these limitations, this study will be the first randomized effort to measure multi-month ART dispensing intervals on the outcomes of retention, virologic suppression, and cost-effectiveness. If 6-month dispensing intervals are proven to be non-inferior and cost-effective, the results may help to inform ART dispensing standard of care guidelines in Malawi, Zambia, and other limited-resource health systems.

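### Cost-effectiveness is compared through each arm's average cost per retained patient, which cannot separate cheaper-and-as-good from cheaper-but-worse; the 6- versus 3-month comparison should be incremental

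*Protocol article*

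**What the plan says.** All references are to the protocol article.

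- **Measure** (Data analysis, Secondary outcomes): "Cost-effectiveness will be assessed as the average cost per patient achieving the primary outcome in each arm".
- **Derivation** (same section): "Using the average cost per patient, we will then estimate the cost per outcome achieved in each arm".
- **Comparison** (same section): "We will compare average cost/patient retained in care across the three study arms, initially at 12 months and again at 24 and 36 months".
- **Uncertainty** (same section): "Costs will be reported as means with 95% confidence intervals and medians with IQRs".
- **Hypothesis** (end of Intervention): 6-month dispensing will be non-inferior to 3-month on retention and virologic suppression, and "6-month intervals will be cost-effective compared to 3-month intervals".
- **Retention contrast** (Primary outcome): risk ratios are estimated "for the effect of each intervention arm compared to standard of care". No 6- versus 3-month estimate is named there.
- **Use of the result** (Discussion): results may inform guidelines "If 6-month dispensing intervals are proven to be non-inferior and cost-effective".

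The article names no difference in cost, difference in retention, incremental ratio, net benefit or threshold for the cost-effectiveness comparison.

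**The concern.** Whether 6-month dispensing is cost-effective compared with 3-month depends on two differences taken together: how much less it costs, and how many fewer or more patients it retains. An average ratio per arm folds both into one number. A lower ratio can mean a cheaper arm with equal retention, or a cheaper arm that retains fewer patients, and the ratio does not say which.

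The Discussion notes that savings from longer intervals are widely expected and calls the economic evaluation essential for resource allocation. Cheaper with somewhat lower retention is therefore a case the plan should be able to describe properly. At stake is a published statement that 6-month dispensing is more cost-effective when all that has been shown is a saving bought with some loss of retention.

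**Working it through.** **1. The plan's own figure.** The article gives no cost figure. Its sample size supplies the retention rates, so that is checked first. Inputs (Sample size): 5% not retained under standard of care, 7.5% as the non-inferior limit, one-sided 0.05, power 90%, ICC 0.004, 10 clusters per arm.

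- Individually randomised: n = 2 × 0.05 × 0.95 × (1.645 + 1.282)² / 0.025² ≈ 1301.7 per arm.
- With k = 10 clusters: m = n(1 − ICC)/(k − n × ICC) = 1301.7 × 0.996/(10 − 5.207) = 270.5, so 271 per cluster and 2710 per arm.

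This reproduces the article's figure. It confirms planning retention of 95% and a 2.5-point margin (95% versus 92.5%), set against standard of care.

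**2. When the average ratio favours the cheaper arm.** Let C be mean cost and R the proportion retained. Then C6/R6 < C3/R3 exactly when the relative saving, 1 − C6/C3, exceeds 1 − R6/R3. Assumptions: R3 = 95% (the article gives no separate 3-month rate) and C3 = 100 index units.

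| R6 | Break-even saving, 1 − R6/0.95 |
|---|---|
| 92.5% | 2.63% |
| 90% | 5.26% |
| 85% | 10.5% |

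In the other direction, the R6 above which 6-month still has the lower ratio is 0.95 × (1 − saving): 92.2%, 90.3%, 85.5% and 76.0% for savings of 3%, 5%, 10% and 20%.

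**3. Average against incremental, worked.** The 3-month ratio is 100/0.95 = 105.3.

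| 6-month cost | R6 | Average ratio | Saved per retained patient lost |
|---|---|---|---|
| 95 | 92.5% | 102.7 | 5/0.025 = 200 |
| 92 | 90% | 102.2 | 8/0.05 = 160 |
| 90 | 90% | 100.0 | 10/0.05 = 200 |

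All three rank ahead of 3-month. The first and third make the same trade per patient lost, yet the one losing 5 points has the better average ratio.

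**4. One ratio, different situations.** A ratio of about 97.3 fits 92.4/0.95 (cheaper, equal retention), 90/0.925 (at the planning limit) and 87.6/0.90 (5 points worse).

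**5. What the ranking implies.** Rearranging step 2 for R6 < R3: 6-month has the lower ratio exactly when (C3 − C6)/(R3 − R6) > C3/R3. Choosing the lower ratio therefore values a retained patient at the 3-month arm's own average cost (105.3 here), a value nobody has chosen or justified.

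**The case against.** Much of the case on the other side is sound.

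- **No decision rule is stated.** A reader might infer that the arm with the lowest ratio is declared the winner. The article says only that the averages will be estimated and compared. This stands.
- **Non-inferiority is required too.** A reader might infer that an arm failing on retention would be recommended because it is cheap. The hypothesis and the Discussion both pair cost-effectiveness with non-inferiority, so an arm at 90% against 95% should fail on the primary outcome. This stands for a clearly worse arm. It does not cover losses inside the margin. The cost-effectiveness text is not itself conditional on non-inferiority. The primary analysis is at 12 months, while the ratios are compared again at 24 and 36.
- **The components are available.** A reader might infer that the trial cannot address its cost-effectiveness hypothesis. Costs are reported with intervals and retention is analysed, so the differences can be obtained from the planned data. The limit lies in the chosen measure, not in the trial.
- **Clustering and joint uncertainty.** A reader might infer that cost intervals will ignore facility clustering. The article does not say so, and a condensed article may leave this to the full plan. That is no finding.
- **The sizes are illustrative.** Costs and 3-month retention are assumed, and the net saving is unknown because the planned inventory includes drugs, laboratory tests, fixed costs and investment in multi-month capacity. The 2.5-point margin is set against standard of care, so calling a 5-point gap between 6- and 3-month twice the margin would borrow it. The algebra does not depend on these values.
- **The outcome is secondary.** The article says secondary aims are not powered. This stands and limits the weight of the point.

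**Conclusion.** The point holds in a bounded form. The article fixes a measure that does not match its comparative hypothesis and cannot distinguish a cheaper arm with equal retention from a cheaper arm with worse retention. Under the assumption of 95% retention at 3 months, savings above 2.6% (at 92.5% retained) or 5.3% (at 90%) are enough for the average ratio to favour 6-month dispensing. If 6-month proves cheaper and at least as well retained, the average and incremental approaches agree and nothing is lost.

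The exposure is therefore a misleading cost-effectiveness statement within the non-inferiority margin, in comparisons with standard of care, and at 24 and 36 months. The primary retention analysis, the sample size and data collection are not affected. The change is worth making because the measure is stated explicitly, so a fuller plan would have to replace it rather than merely add detail.

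**What to change.** Make the cost-effectiveness comparison incremental.

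- For 6-month versus 3-month, and for each versus standard of care, report the difference in mean cost and the difference in proportion retained together, at 12, 24 and 36 months.
- Summarise them as incremental cost per additional patient retained or as net benefit. Where non-inferiority has been shown for that contrast and time point, a cost difference alone is enough. For 6-month versus 3-month this requires stating the margin that applies, because the sample size sets one only against standard of care.
- Give intervals that respect facility clustering and reflect cost and retention jointly, for example from a bootstrap that resamples facilities.
- Keep average cost per retained patient in each arm as a descriptive figure.

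The cost is revised wording in the analysis section and a little more programming. No new data, participants or design change are needed.

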### Intervention

This study will compare standard of care to two alternative dispensing strategies. Under standard of care, ART dispensing intervals are based on provider opinion. Malawi and Zambia ART guidelines recommend 3-month dispensing for stable patients, but adherence to guidelines is variable and dispensing may vary due to provider and/or patient preference or medication availability. Participants in the 3-month dispensing study arm will receive a 90-day supply of ART and will have routine clinic visits every 90 days. Participants in the 6-month dispensing study arm will receive a 180-day supply of ART and will have routine clinic visits every 180 days. For all arms, other HIV services will be standard of care and supplies of co-trimoxazole (CPT) and isoniazid (IPT) will also be provided based on the assigned ART dispensing interval and country-specific guidelines about use of these therapies as part of routine HIV care.

Pharmacy support will be provided as part of the study, to ensure medication stock outs do not occur at study sites and that study sites do not take drug stocks away from non-study facilities. The trial is being conducted in close collaboration with the Ministries of Health in Malawi and Zambia and USAID, with support from the Supply Chain Management Systems (SCMS). Participants in the 6-month arm will be offered generic plastic bags to assist with carrying the large supply of medications. Participants will be given information about “ideal” basic storage conditions for medications, particularly in regard to temperature and avoidance of storage in direct sunlight. Participants who provide written informed consent will be willing to participate in any of the study arms; however, those in the 6-month arm may request a reduction in refill duration at any point during follow up. The proportion of individuals changing from 6-month ART dispensing to shorter intervals and reasons for changing will be captured during follow up.

To measure the primary outcome of retention, data will be abstracted from participants’ medical records. In Malawi and Zambia, default from care is defined as being out of ART for more than 60 days, and this definition will be used for the endpoint of retention (<60 days without ART at each time point).

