#### Eligibility screening

Patients will be provided general information about the study in ART clinic waiting areas and recruited by a study staff representative. Interested patients will be taken to a private space with a study staff representative to learn about the study, provide oral consent, undergo anonymous screening procedures, and, if eligible, provide written informed consent. A recent viral load test (within 6 months of the entry visit date) is required to determine eligibility; however, we anticipate many participants will not have a recent viral load result available at the time of screening. For participants who do not have a viral load documented, a sample will be collected after written informed consent is obtained, but the participant will not be enrolled in the study until the test results have been received. Patients who have a viral load sample drawn for study eligibility will receive test results during their next routine visit and will repeat the screening survey at that visit to ensure there have been no changes in eligibility criteria over the interim period.

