## Trial status

This manuscript was developed using study protocol version 2.4, 22 June 2017, for “The INTERVAL Study: Varying Intervals of ART Dispensing to Improve Outcomes in HIV”. Recruitment and enrollment began 31 May 2017. Enrollment is expected to be completed by 30 November 2017.

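### The one-month windows of the clinic-level access proxy are shorter than a 6-month dispensing cycle, so the count mixes dispensing interval with site enrolment timing

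*Protocol article*

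**What the plan says.** Under Data analysis, Secondary outcomes, the protocol article says that "we will explore clinic resource allocation to determine the effects of the dispensing interval on patients’ access to care". It offers two proxies. The first is waiting time or total time in clinic, compared by arm. The second is the one at issue: "we will use aggregate, clinic-level data to ascertain whether the quantity or mix of services provided by each study site" has shifted. The comparison looks at "changes between the last month before the start of the study and the first month of year 2 of the study". A general caveat follows: "While neither of these measures is a perfect indicator of access, both will provide some indication of the availability" of HIV and non-HIV care.

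The visit cycles are set under Intervention. Participants in the 3-month arm "will receive a 90-day supply of ART and will have routine clinic visits every 90 days"; those in the 6-month arm "will receive a 180-day supply of ART and will have routine clinic visits every 180 days". Trial status gives the timing: "Recruitment and enrollment began 31 May 2017. Enrollment is expected to be completed by 30 November 2017".

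The article does not say whether the start of the study is study-wide or site by site. If it means first enrolment overall, the two windows are about 1 to 30 May 2017 and 31 May to 29 June 2018.

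**The concern.** The proxy is meant to show whether longer dispensing intervals change what a clinic can provide. A one-month count contains only those study participants whose routine visit falls in that month. In the 6-month arm that is about one sixth of a cycle, and the site's enrolment dates decide which sixth.

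Nothing in the design makes enrolment even over time, and Eligibility screening points away from it. Many patients are expected to lack a recent viral load, and for them "the participant will not be enrolled in the study until the test results have been received", with entry at the next routine visit. A group deferred by roughly one routine interval could be due in the window in the 3-month arm and not in the 6-month arm.

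A before-after change at a single site also picks up whatever else moved in between, such as growth of the ART cohort or the isoniazid rollout in Malawi that the Discussion anticipates. At stake is an exploratory reading of whether 6-month dispensing frees clinic capacity, in a trial intended to inform policy.

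**Working it through.** **The plan's own figure.** The article gives no number for this measure. The one figure borrowed here is 271 participants per cluster (Sample size), which reproduces. With 5% failure in both arms, a 2.5-point margin, one-sided 0.05 and 90% power, n = 1301.7 per arm before clustering. With 10 clusters per arm and ICC 0.004, m = 1301.7 × 0.996 / (10 − 1301.7 × 0.004) = 270.5, rounded up to 271.

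**Inputs.**
- Enrolment on days 0 to 183 after 31 May 2017 (Trial status).
- Routine visits every 90 or 180 days after entry (Intervention).
- First month of year 2 = days 365 to 394.
- Assumed: visits on schedule, everyone retained, and the same accrual pattern in both arms.

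**Who is due.** A participant entering on day d has visits at d + 180j (6-month arm) or d + 90j (3-month arm).
- 6-month arm: d + 360 falls in the window for d = 5 to 34. No other visit can.
- 3-month arm: d + 360 falls in it for d = 5 to 34, and d + 270 for d = 95 to 124.

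Let E1 be the share entering on days 5 to 34 and E2 the share entering on days 95 to 124. Visits per participant are then E1 (6-month) and E1 + E2 (3-month). The ratio is E1 / (E1 + E2) and the difference is E2. The long-run values for 271 participants are 271 × 30/180 = 45 and 271 × 30/90 = 90 visits a month, a ratio of 0.50.

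**Results under assumed accrual patterns, per site of 271.**

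| Pattern | E1 | E2 | 6-month visits | 3-month visits | Ratio | Difference |
|---|---|---|---|---|---|---|
| Uniform, days 0–183 | 0.163 | 0.163 | 44 | 88 | 0.50 | 44 |
| Falling linearly | 0.291 | 0.131 | 79 | 114 | 0.69 | 35 |
| Rising linearly | 0.035 | 0.195 | 9 | 62 | 0.15 | 53 |
| All in days 0–89 | 0.333 | 0 | 90 | 90 | 1.00 | 0 |
| All in days 90–182 | 0 | 0.323 | 0 | 87 | 0 | 87 |

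Example, falling pattern: the weight is 1 − d/183, which sums to 92. Days 5 to 34 give 30 − 585/183 = 26.80, and 26.80/92 = 0.291. Days 95 to 124 give 30 − 3285/183 = 12.05, and 12.05/92 = 0.131.

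**A mechanism that the protocol itself suggests.** Assume screening spread evenly over 91 days, a share f with a viral load on file who enter at once, and the rest entering 90 days later. Then E1 = f × 30/91 and E2 = (1 − f) × 30/91, so the ratio equals f. With f = 0.3 the counts are 271 × 0.3 × 30/91 = 27 against 271 × 30/91 = 89. Only f = 0.5 gives 0.50. The article gives neither f nor the length of the wait.

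**Full-cycle window.** Any 180 consecutive days from the start of year 2 contain exactly one 180-day visit or two 90-day visits per participant, whatever the entry day. The result is 1.00 against 2.00, a ratio of 0.50 under every pattern.

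**The case against.** The case on the other side is substantial, and most of it limits the size of the point.

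- **Uniform enrolment gives the right answer.** A reader might infer that the measure captures enrolment timing instead of dispensing interval. The documents do not support that: even accrual over the planned six months returns 0.50. Timing is mixed with interval and does not replace it.
- **The measure counts all clinic services.** A reader might take the ratios above as the fall in activity that a clinic would report. They are not. The count includes non-study ART patients and non-HIV care, and the article gives no facility volume. In absolute terms the linear patterns move the between-arm difference from 44 visits a month to 35 or 53, about a fifth either way, within a whole clinic's count. The real interval effect on visits comes through the same participants, so other care dilutes both and does not remove the distortion.
- **The accrual patterns are assumed.** Only start and expected end dates are given. Requests for shorter refills in the 6-month arm and extra isoniazid visits in Malawi would also spread visits beyond the modelled days.
- **Season.** The months are adjacent, about May against June, so a strong seasonal bias is not a fair inference. Matched sites randomised to the three arms share the calendar if arms are compared.
- **Visits are measured properly elsewhere.** Follow-up data collection records each participant's visits, and the patient-cost analysis counts them per 12-month period. The fall in participants' own visits does not depend on this proxy.
- **It is exploratory and caveated, and averaged over 10 sites per arm.** Averaging reduces haphazard site differences. It does not remove a pattern common to all sites, such as the wait for viral load results.

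What remains is that the two single months are a stated choice, not a detail left to another document, and that the general caveat does not mention window length or enrolment timing.

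**Conclusion.** The point holds as a limited weakness of one exploratory proxy. Each window covers about one sixth of the 6-month cycle, so the study participants' contribution depends on when the site enrolled. With on-schedule visits and the same accrual pattern in both arms, the 6-month to 3-month ratio of routine visits in the first month of year 2 can lie anywhere from 0 to 1 against a true 0.50. It is 0.69 or 0.15 under linearly falling or rising enrolment, and 0.50 under uniform enrolment. The size of the distortion in total clinic volume cannot be derived from the document. No primary outcome, sample-size figure or stopping rule rests on this measure.

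**What to change.** Replace each single month with at least six consecutive months of routine aggregate counts, one full 180-day cycle, using the same calendar months before the study and in year 2. On the stated dates, June to November 2016 against June to November 2018 would do, or December 2016 to May 2017 against December 2018 to May 2019. State whether the start of the study is study-wide or per site. State also that the before-after change will be compared between arms within the matched sets, so that shared trends cancel.

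The cost is 30 sites × 2 periods × 6 months = 360 site-months of reports instead of 30 × 2 = 60, six times as many. The result for this measure also comes at least five months later. No new patient contact is needed.
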